Over the years, there have been other non-pharmacological approaches showing promising results. A recent review by Chan et al. (2021) on non-pharmacological interventions in insomnia mentions mindfulness or Tai Chi as possible alternatives or complementary practices to treat sleep disturbances. Nevertheless, the objective of these practices is comparable to the relaxation/meditation component of CBT-I, seeking better knowledge and perception of internal and external stimuli, a greater focus on attentional processes, and, therefore, an improvement in the inhibition of other stimuli considered irrelevant or potentially harmful. Currently, both mindfulness and Thai Chi interventions have functional digital support applications. However, as in the case of CBT-I, adherence and therapy commitment are compromised due to complexity, abstraction, patient reluctance, and low level of motivation (Li et al., 2004; Ong et al., 2014; Black et al., 2015).

As the key component of insomnia seems to be hyperarousal and executive function deficit, interventions that enhance cognitive functioning (primarily inhibition mechanisms and attentional processes) might effectively reduce brain hyperactivation and distorted attentional stimulus focus. Even though the CBT-I might entail cognitive skills training, its main purpose is to restructure distorted cognitive beliefs and give the patient comprehensive safety behaviors, leaving aside the cognitive functioning alterations (i.e., attention, memory, and executive functions) present in patients with insomnia. In this sense, in recent years, computerized cognitive training (CCT) programs that reinforce the neural connections of the cognitive mechanisms underlying attentional control and inhibitory processes have been proposed as a successful method to directly focus on the dysfunctional cognitive mechanisms by stimulating the critical memory and attention cognitive domains, resulting in better ease of falling asleep.

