Next, the CCT intervention will be carried out. This will be done through the CogniFit online platform so that each participant will access it from home using a personal computer or smart device. The training will last for a total of 8 weeks, with five training days per week. This way, a total of 40 training sessions are expected. The duration of the sessions will be determined by the maximum tolerated training time resulting from the phase-I trial. Since this process will be autonomously managed by each participant, they will be contacted periodically (a minimum of two phone calls per week) to ensure adherence and check that they have not had any incidence. The platform will record participants’ performance, providing researchers with real-time feedback on the performance and adherence of each participant.

Participants will be randomly assigned to one out of two groups (control/experimental). The experimental group will complete a personalized CCT intervention based on CogniFit’s Personalized Online Training, including a series of games and activities targeting attention, memory and executive functions. The difficulty level of each of the activities will dynamically change to match the cognitive profile of each participant on each training day. By automatically adjusting the activities’ difficulty and requirements according to each participant’s performance, cognitive taxing is adapted and a maximum cognitive effort is always required. Similar to Haimov and Shatil (2013), the active control group will complete a series of painting activities specifically designed not to result cognitively demanding and to maintain a low complexity level and constant difficulty throughout the intervention. These activities will not target the intended cognitive processes (namely, they will target orthogonal unrelated aspects). Participants will be randomly assigned to either the experimental or control group, with the experimenters and the patients being fully blind to the group classification.

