After post-test data collection, and prior to statistical analyses, all variables will be checked for normality of distribution, and plots will be visually inspected for asymmetry and kurtosis. Then, descriptive statistics will be obtained to provide an overview of the sociodemographic and clinical characteristics of the participants. To examine intervention effectiveness, the changes in all outcome measures from baseline (pretest) to post-intervention (post-test) will be analyzed. Differences in primary outcomes and secondary outcomes will be analyzed through linear mixed models for repeated measures. Models will assess within and between-group differences before and after the intervention. The Group factor (experimental, control) will be included as an independent variable, together with Time (pre-test at baseline, post-test after the intervention). Sociodemographic factors such as gender and age will be used as moderators. Dependent variables will be sleep quality, insomnia severity, quality of life, cognitive abilities, executive function, depressive symptoms, anxiety symptoms, and worrying. To isolate the variable that better explains the model, a hierarchical regression analysis will be conducted with the sleep quality improvements as the dependent variable and the cognitive improvements as the independent ones. This hierarchical regression analysis will be also useful to evaluate the impact of the adherence to the training in the whole sample of participants, regardless of whether they have effectively completed the intervention or not (i.e., cases of attrition or incomplete sessions). The hierarchical regression analysis with the sleep quality improvement as the dependent variable will follow a stepwise approach in which sociodemographic factors will be added in a first step, the data corresponding to the adherence to the treatment (namely, number and length of the completed sessions) in a second step, and the cognitive data from the BRIEF-A and the Cognitive Assessment Battery CAB™ as a third and final step.

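### The Phase III adherence regression, read as pooling both arms, counts painting sessions as training dose and mixes a diluted training effect with self-selection, so its coefficient is not an impact of adherence

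*Protocol article*

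**What the plan says.** The Phase III analysis text in the protocol article describes two separate analyses.

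- **Effectiveness.** Linear mixed models with Group and Time, for primary and secondary outcomes. This is the randomised comparison.
- **Hierarchical regression.** The dependent variable is the improvement in sleep quality. The three steps are given in order: "sociodemographic factors will be added in a first step"; then "the data corresponding to the adherence to the treatment (namely, number and length of the completed sessions) in a second step"; then "the cognitive data from the BRIEF-A and the Cognitive Assessment Battery CAB™ as a third and final step".

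The regression is meant mainly to find which cognitive gains explain the sleep gain, but it is given a second use: "This hierarchical regression analysis will be also useful to evaluate the impact of the adherence to the training in the whole sample of participants". The sample for that use is explained by completion: "in the whole sample of participants, regardless of whether they have effectively completed the intervention or not".

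The same Phase III text describes how sessions come about. On the schedule: "This way, a total of 40 training sessions are expected". On conduct at home: "Since this process will be autonomously managed by each participant", with at least two phone calls a week to support adherence. The control arm does painting of low, constant difficulty that is not aimed at the trained cognitive processes.

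**The concern.** Two features of the stated regression stop its session coefficient from being an impact of adherence.

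1. **The dose is mislabelled.** If both arms are pooled, a completed painting session and a completed CCT session enter as the same unit of treatment, although only one of them trains the targeted functions. This distorts the slope without any confounding.
2. **The exposure is self-selected.** Nobody is randomised to a number of sessions, and both arms have the same prescribed schedule. Any trait that affects both persistence and self-reported sleep gain enters the slope, and sociodemographic factors remove it only so far as they capture that trait. The article ties adherence to motivation for other non-drug approaches (on mindfulness and Tai Chi: "adherence and therapy commitment are compromised due to complexity, abstraction, patient reluctance, and low level of motivation"). It does not say this of CCT, but the mechanism is plausible there too.

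At stake is the only analysis in the Phase III text that uses training received. The sample-size section expects attrition and non-adherence, so sessions will vary. The trial could report a benefit of adherence when training does nothing, or miss a real one.

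**Working it through.** The plan gives no adherence coefficient to reproduce. Its 60 participants per group come without an effect size, SD or numeric power, and that figure is not in dispute here.

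**Inputs from the article:** 60 per arm, 40 planned sessions, PSQI range 0-21, two-sided 5% test.

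**Assumptions, not in the article:** sessions roughly normal, mean 30, SD 8, limited to 0-40; SD of PSQI gain 3; painting sessions have no effect; an unmeasured trait correlates rho with both sessions and gain; true CCT effect beta = 0 or 0.05 points per session. Session length and the sociodemographic covariates are left out.

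**Step 1: dilution.** Write A for sessions, G for arm (1 = CCT), and gain = constant + beta x A x G + error. With equal arms,

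Cov(A, A x G) = 0.25 x (m1 - m0) x m1 + 0.5 x v1

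where m1 and m0 are the arm means and v1 is the variance of sessions in the CCT arm. The pooled slope is beta x Cov(A, A x G) / Var(A).

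- Equal adherence: 0.05 x (0.5 x 64) / 64 = 0.025, half the true 0.05.
- CCT arm 6 sessions lower (24 against 30): Cov = 0.25 x (-6) x 24 + 0.5 x 64 = -36 + 32 = -4; Var(A) = 64 + 0.25 x 36 = 73; slope = 0.05 x (-4/73) = -0.003. Simulated: -0.004.
- A Group main effect alone removes the between-arm part but leaves the common slope at about 0.05 x 32/64 = 0.025. The interaction is needed to separate the two kinds of session.

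**Step 2: self-selection.** The trait adds (8 x rho) x (3 x rho) / 64 = 0.375 x rho² to the slope: 0.034 at rho = 0.3 and 0.094 at rho = 0.5.

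**Step 3: both together** (4,000 simulated trials per row, pooled, no group term, complete data):

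| True effect | rho | Algebra | Simulated slope | Significant |
|---|---|---|---|---|
| 0 | 0 | 0 | 0.000 | 5% |
| 0 | 0.3 | 0.034 | 0.036 | 16% |
| 0 | 0.5 | 0.094 | 0.101 | 78% |
| 0.05 | 0 | 0.025 | 0.026 | 10% |
| 0.05 | 0.3 | 0.059 | 0.061 | 34% |
| 0.05 | 0.5 | 0.119 | 0.128 | 92% |

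The cap at 40 sessions makes the simulated slopes slightly larger than the algebra. In the fourth row the arm difference is 1.48 points, or 1.48/3 = 0.49 SD, yet the pooled slope is significant in only 10% of trials.

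**Step 4: check under a second set-up.** With a common trait loading of 0.3 on standardised adherence and gain and no true effect, the pooled slope is significant in 17% of trials. Adding a Group term leaves it at 17%, and the Group x sessions term rejects in about 5%. At a loading of 0.4 the figures are 42%, 41% and 5%. Here self-selection is the same in both arms.

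**Step 5: CCT arm only.** If only that arm were used, the dilution goes but the selection stays: at rho = 0.5 the slope is 0.153 against a true 0.05.

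**The case against.** **The article does not say that both arms are pooled.** It explains the whole sample by completion, not by arm. That is fair, but pooling is the natural reading, and Step 5 shows that the narrower reading still leaves the self-selection.

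**A group term and baseline score could be left to the full analysis plan.** This would stand if the regression were only mentioned. The article instead lists outcome, predictors and order, and attaches a causal word to the result. The point concerns a stated analysis, not a missing detail.

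**Little rests on the coefficient.** This largely stands. A reader might infer that the efficacy conclusion is at risk. It is not: effectiveness is judged by the Group and Time model, adherence is a by-use of the regression, and the number of sessions needed is a Phase II question.

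**A reader might infer that the slope shows only who keeps going.** That is too absolute. Without self-selection it still carries about half the training effect, so it is a mixture. Adherence is also not left wholly to the participant, given the regular calls.

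**A reader might infer that the randomised arms would give an unbiased estimate of the adherence effect.** They do not. They estimate the effect of assignment, which is already planned. An instrumental-variable estimate with control set to zero CCT sessions and no covariates is that difference divided by mean CCT sessions. If a benefit of 0.50 SD were complete by session 10 and later sessions added nothing, it would still report 0.50 SD per 30 sessions. If assignment alone gave 0.30 SD, through expectation for example, it would report 0.30. It also inherits bias from selective dropout: in one simulated case (rho 0.5, dropout in the CCT arm related to motivation) the complete-case arm difference was 0.57 points when the truth was 0.

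**Comparing slopes between arms is not a full cure.** This stands. CCT demands maximum effort and painting does not, so selection may differ. With no true effect, trait-adherence correlations of 0.5 (CCT) and 0.2 (painting) and a trait-gain correlation of 0.5, the Group x sessions term was significant in 13% of trials. With 0.6, 0.2 and 0.6 it was 27%.

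**Conclusion.** The point holds for the adherence regression and goes no further. As written, and pooled over arms, the step-2 coefficient is about half the true CCT slope when adherence is equal and nothing confounds it. It can disappear when the CCT arm completes somewhat fewer sessions. These results need only that painting sessions have no effect on sleep; the article itself allows a minor improvement in controls.

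Self-selection adds a further term of unknown size. The false-positive rates of about 16-17% at correlations of 0.3, and 78% at 0.5, depend on assumed correlations and an assumed spread of sessions. That some bias exists needs only one shared cause of adherence and sleep gain. Its direction is also unknown: if patients who improve on their own stop early, the slope can turn negative.

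The word impact is therefore not supported for this coefficient. The randomised efficacy analysis is unaffected.

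**What to change.** - **Step 1:** add Group and pretest PSQI to the sociodemographic factors.
- **Step 2:** add completed sessions and Group x sessions, and report the session slope separately for each arm.
- **Wording:** call these results exploratory associations. State that the CCT slope minus the painting slope removes self-selection only if selection is similar in both arms.
- **Optional sensitivity analysis:** if an effect of training received is wanted, prespecify an instrumental-variable (complier-average) estimate with allocated arm as instrument. State its exclusion and linearity assumptions and its need for adequate post-test data. State also that it does not show whether more sessions help more.
- **Efficacy:** leave the Group and Time model as it is.

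The cost is a few lines of analysis text and one or two extra terms. The platform already records performance and adherence, and PSQI is measured at pretest. The price is wider intervals for the arm-specific slopes, each estimated from about 60 participants at most if the minimum sample is enrolled.

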### Participant Selection and Sample Sizes

Participants will be recruited from the Sleep Unit of the Hospital Universitario de la Ribera (Spain) for the phase-I and phase-II trials, and from the same Unit and associated medical centers for the phase-III trial. According to the *a priori* established eligibility criteria, participants will be adults between 25 and 55 years old who have been diagnosed by Insomnia Disorder according to DSM-5, fully matching the diagnostic criteria (e.g., showing a predominant complaint of dissatisfaction with sleep quantity or quality occurring at least three nights per week and having been present for a minimum of 3 months, despite them having adequate opportunity for sleep and in the absence of sleep-wake disorders or the use of substances, which causes clinically relevant impairment). We selected this age range in an attempt to improve sample homogeneity in executive function development (see Ferguson et al., 2021), and to ensure that participants would have access to new technologies. Participants will be excluded from the study if they meet any of the following *a priori* established criteria: (1) they present another sleep-wake disorder (e.g., narcolepsy, restless leg syndrome, a breathing-related sleep disorder, a circadian sleep-wake rhythm disorder, a parasomnia); (2) they present a relevant medical, psychiatric or neurological disorder; (3) they show significant visual or motor impairments; (4) they present history of alcohol or drug abuse or dependence; (5) they show a caffeine consumption higher than 150 mg per day or an alcohol consumption higher that 250 ml per day; (6) they use medication with stimulant action, except the sedatives or hypnotics specifically prescribed for sleep.

The phase-I trial will follow a standard 3 + 3 protocol. Consequently, the minimum number of participants will be three, and the maximum number of participants will depend on the results of each of the 3-patient cohorts. The phase-II trial will include 20 insomnia patients. Finally, the phase-III trial will consist of a minimum sample size set at 60 participants per group, given that the purpose of this research is to make a first approach to the positive impact of a cognitive training of executive functions on insomnia and to be able to generalize the results obtained with a 95% confidence interval and sufficient statistical power to test hypotheses (sig. bilateral). While a larger number of participants would be desirable for a phase-III trial, it should be considered that the specific selection criteria of the sample and the restricted number of patients that are available at the hospital and the associated centers make it difficult to increase the sample size to account for potential attrition rates and lack of adherence.

### Instruments and Outcome Measures

We will carry out a specific evaluation of sleep quality and insomnia, together with a general evaluation of the participant’s neurocognitive and emotional state. Likewise, these evaluations will be complemented with an assessment of the quality of life.

#### Primary Outcome Measures

##### Sleep Quality

The Pittsburgh Sleep Quality Index (PSQI) will be used. The PSQI is a self-report questionnaire that assesses sleep quality and consists of 19 individual items, creating seven components that produce one global score. It takes 5–10 min to complete. The PSQI includes a scoring key for calculating a patient’s seven sub-scores, each of which can range from 0 to 3. The sub-scores are tallied, yielding a global score that can range from 0 to 21. A global score of five or more indicates poor sleep quality, and the higher the score is, the worse the sleep quality can be considered.

##### Insomnia Severity

The Insomnia Severity Index (ISI) will be used. The ISI is a brief instrument designed to assess the severity of both nighttime and daytime components of insomnia. It comprises seven items assessing the perceived severity of difficulties initiating sleep, staying asleep, early morning awakenings, satisfaction with current sleep pattern, interference with daily functioning, noticeability of impairment attributed to the sleep problem, and degree of distress or concern caused by the sleep problem. Possible scores range from 0 (no clinically significant insomnia) to 28 (clinical severe insomnia).

##### Quality of Life

The Measuring Quality of Life | The World Health Organization–abridged version (WHOQOL-BREF) will be used. The WHOQOL-BREF is a generic questionnaire to measure the quality of life created by the Study Group on Quality of Life of the World Health Organization. It has two general questions on the quality of life and satisfaction with the state health, and 24 questions grouped into four areas or domains: Physical Health, Psychological Health, Social Relations, and Environment. The measure is calculated by summing the scores in the questions corresponding to each domain and then transforming them to a 0–100 point interval. Possible scores for each domain range from 0 (poor perceived quality of life) to 100 (greater perceived quality of life).

Additionally, the short version of the self-perceived global physical and mental health scale from the Patient-Reported Outcomes Measurement Information System (PROMIS v.1.2; see (Hays et al., 2015, 2017), will be also used. Participants will respond to the following questions: *In general, how would you rate your health?* (Options: Excellent, Very Good, Good, Fair, Poor); *In general, how would you rate your physical health?* (Options: Excellent, Very Good, Good, Fair, Poor); *To what extent are you able to carry out your everyday physical activities such as walking, climbing stairs, carrying groceries, or moving a chair?* (Options: Completely, Mostly, Moderately, A little, Not at all); *In general, how would you rate your mental health, including your mood and your ability to think?* (Options: Excellent, Very Good, Good, Fair, Poor); *In general, how would you rate your satisfaction with your social activities and relationships?* (Options: Excellent, Very Good, Good, Fair, Poor).

#### Secondary Outcome Measures

##### Executive Functions

The Behavior Rating Inventory of Executive Function-Adult Version (BRIEF-A) will be used. The BRIEF-A is a standardized measure that captures views of an adult’s executive functions or self-regulation in his or her everyday environment. Only the self-report format will be used. The BRIEF-A comprises 75 items within nine theoretically and empirically derived clinical scales that measure various aspects of executive functioning; Inhibit, Self-Monitor, Plan/Organize, Shift, Initiate, Task Monitor, Emotional Control, Working Memory, Organization of Materials. The clinical scales form two broader indexes: Behavioral Regulation (BRI) and Metacognition (MI), and these indexes form the overall summary score, the Global Executive Composite (GEC). It also includes three validity scales (Negativity, Inconsistency, and Infrequency). It takes approximately 10–15 min to administer. All 75 items are rated in terms of frequency on a 3-point scale: 0 (never), 1 (sometimes), 2 (often). Raw scores for each scale are summed for the total score.

##### Cognitive Skills

The Cognitive Assessment Battery CAB™ test provides a general cognitive score as well as specific scores in each of the measured cognitive skills. The Cognitive Assessment Battery CAB™ includes a series of 17 short tests (∼2–3 min each) that measure a variety of different cognitive abilities, putting a heavy focus on executive functions. These are then used to obtain a general score, as well as five different sub-scores based on perception, attention, memory, coordination and reasoning. The resulting scores per participant in each of the 23 cognitive skills measured by the CAB™ are contrasted with the normative database of the test and each converted into z-scores and percentiles. It takes about 40 min to administer when done for the first time prior to any form of computerized training, and then it automatically updates the information and scores by recalculating the output as a function of participants’ performance in the tasks included in CogniFit’s Personalized Online Training.

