#### Phase II

This trial will include a different group of 20 patients from the same hospital who meet the inclusion criteria described above, who will also sign the corresponding consent forms prior to initiation of collaboration. After having set the maximum tolerated training time per session in the phase I trial, a 15-day phase-II trial will be designed to ascertain the effectiveness of the CCT in the absence of adverse events or side effects.

To this end, 20 patients from the Sleep Unit of the Hospital Universitario de la Ribera (Spain) will be recruited and they will first complete an initial session (Day 1) that will serve to collect baseline data about their sleep problems and their cognitive skills, as well as about their sociodemographic information. As in the phase I trial, they will complete the general cognitive and psychological evaluation lasting for around 60 min (see Instruments and Outcome Measures section).

The day after the initial evaluation (Day 2), participants will be asked to visit the Sleep Unit again to complete the first training session with the CCT. The duration of the training session will be determined by the results of the phase I trial. Participants will complete this training session using either a tablet, a PC or a laptop, accompanied by the research and clinical team. Right at the end of the session, and in order to assess the safety of the intervention, participants will also complete the same safety questionnaire as in the phase I trial. In case any participant at any moment would report potential adverse events in any of the safety questions, the clinical psychologist would immediately interview them in order to classify the side effect or adverse event according to its seriousness following the criteria and elements adapted from the Patient-Reported Adverse Drug Event Questionnaire (de Vries et al., 2013).

The protocol would then continue the next day (Day 3) with a full assessment identical to that of the first session. The day after (Day 4) would consist of the repetition of the training session of Day 2. This way, and alternating assessment and training sessions, participants will complete a 15-day cycle that will start and end with a full assessment (Day 1 and Day 15), and that will include eight different evaluation or test points (Day 1, Day 3, Day 5, Day 7, Day 9, Day 11, Day 13, and Day 15) and seven training sessions (Day 2, Day 4, Day 6, Day 8, Day 10, Day 12, and Day 14).

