#### Phase III

The final stage of the protocol will consist of a double-blind randomized controlled phase-III trial in which a large group of patients with insomnia recruited from the Sleep Unit of the Hospital Universitario de la Ribera, as well as from collaborating medical institutions will voluntarily enroll in an 8-weeks personalized and supervised cognitive training intervention. The medical team will inform those patients who meet the inclusion criteria of the possibility of voluntarily participating in the experiment. Those interested will be put in contact with the researchers, who will interview them individually. In this first contact, all the information regarding the study will be provided. Patients who agree to participate will complete the necessary legal documentation and informed consent and be included in the study.

A complete evaluation will be carried out at the beginning (pretest) and at the end of the intervention (post-test) using the materials and instruments also used in the phase-II study. The pretest will collect baseline data about sleep problems and cognitive skills, together with sociodemographic information. Standardized batteries and tests will be used to measure the general neurocognitive state and the emotional state, together with specific tests and measurements of the pattern and quality of sleep, and tests that measure health-related quality of life. All variables will be measured objectively (i.e., direct test scores) and subjectively (i.e., what the patient or her close associates express). The post-test will collect data on sleep problems and cognitive skills, but no additional sociodemographic data will be needed (see *Instruments and Outcome Measures* section for a description of the tools). Having already established the safety of the protocol in the phase-I and phase-II studies, no information will be collected in this regard in the phase-III trial.

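### The scoring rule for the cognitive battery (CAB) conflicts with the planned re-assessment and, if followed, would measure the post-test CAB differently in the two Phase III arms

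*Protocol article*

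**What the plan says.** All references are to the protocol article.

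- **Cognitive Skills (Secondary Outcome Measures).** The CAB has 17 short tests and yields a general score, sub-scores and scores for individual skills. On duration: "It takes about 40 min to administer when done for the first time prior to any form of computerized training". After that first use the battery "automatically updates the information and scores by recalculating the output as a function of participants’ performance in the tasks included" in CogniFit's training programme.
- **Phase III, intervention.** "The experimental group will complete a personalized CCT intervention based on CogniFit’s Personalized Online Training". For the comparator, "the active control group will complete a series of painting activities specifically designed not to result cognitively demanding", and "These activities will not target the intended cognitive processes (namely, they will target orthogonal unrelated aspects".
- **Phase III, evaluation.** "A complete evaluation will be carried out at the beginning (pretest) and at the end of the intervention (post-test"), with the Phase II instruments. The same paragraph says that objective measurement means scores taken directly from tests.
- **Phase II.** After the first training session, "The protocol would then continue the next day (Day 3) with a full assessment identical to that of the first session". Assessment and training then alternate to Day 15.
- **Phase III, analysis.** Cognitive abilities are a dependent variable in the mixed models with Group and Time. The CAB data, with the BRIEF-A, form the third and final step of the hierarchical regression on sleep quality improvement.

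**The concern.** A pre/post comparison between arms needs the outcome to be obtained in the same way in both arms and at both times. The only text on how the CAB is scored after baseline ties the score to play in the training programme, and only one arm plays it. A Group-by-Time difference in CAB could then mix three things: real change in cognition, task-specific practice on the games, and a change of scoring source that occurs in one arm only.

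The Introduction concedes that evidence for far transfer from cognitive training is limited, so separating practice from transfer matters here. The Expected Results section predicts a between-group gain in cognitive performance, and this scoring could produce one without transfer. In the regression, the CAB change would partly reflect training exposure and would mean different things in the two arms, although the step is there to show which cognitive gains go with better sleep.

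Phase II has one group, so no between-arm bias can arise there. The issue is a change of scoring source after Day 1, together with practice. It bears on the minimum number of sessions wherever that judgement uses the CAB.

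**Working it through.** **1. The passages side by side**

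| Question | Cognitive Skills section | Phase III / Phase II design text |
|---|---|---|
| How is the baseline CAB obtained? | Direct battery, about 40 min, before any training | Part of the pretest or Day 1 evaluation (around 60 min in Phase II) |
| How is the later CAB obtained? | Recalculated from play in the training programme | Complete evaluation with direct test scores (Phase III); assessment identical to the first (Phase II) |
| Who generates the data for the update? | Anyone using the training programme | Phase III: experimental arm only. Phase II: all 20 patients |

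The design text does not name the CAB when it describes the repeat assessment, and it does not say that the automatic update is switched off or ignored. The Cognitive Skills text does not say which score is analysed. The two descriptions cannot both define the post-test CAB.

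**2. What follows from each reading**

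- *Update rule governs.* The experimental post-test CAB comes from the practised games. Controls produce no such data, so their score either stays as it was or comes from a route that the protocol does not describe. In both cases the measurement method differs by arm.
- *Design text governs.* Both arms retake the battery and are scored alike. The analysis must then use the fresh result and not the platform's updated one, and the protocol does not say so.

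**3. Size (illustration only)**

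The plan states no figure that could be reproduced. The sample size of 60 per group has no effect size, SD or power attached.

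Inputs: n = 60 per arm and two-sided 5% (from the 95% confidence and bilateral testing in Participant Selection and Sample Sizes). Assumed: no true difference, and a measurement-only shift of d SD in favour of the trained arm. The documents do not give d.

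Standard error of the difference in SD units: √(2/60) = 0.1826.

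Chance of a significant result (normal approximation): Φ(d/0.1826 − 1.960) + Φ(−d/0.1826 − 1.960).

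| d (SD) | d/0.1826 | Normal approximation | t-test, 118 df |
|---|---|---|---|
| 0 | 0 | 5.0% | 5.0% |
| 0.1 | 0.548 | 8.5% | 8.4% |
| 0.2 | 1.095 | 19.5% | 19.2% |
| 0.3 | 1.643 | 37.6% | 37.1% |
| 0.5 | 2.739 | 78.2% | 77.5% |

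For d = 0.3: Φ(1.643 − 1.960) = Φ(−0.317) = 0.3757. The other tail adds 0.0002, giving 0.3759.

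These are power figures for chosen shifts. They show how quickly a measurement artefact would turn into a positive finding; they do not show that one of this size exists.

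**The case against.** The strongest reply is that the Cognitive Skills sentence describes how the commercial product behaves and does not define the trial's post-test value. The design sections promise a complete evaluation with direct test scores and, in Phase II, an assessment identical to the first. The Phase II evaluation of around 60 minutes leaves room for a 40-minute battery. On that reading both arms take the same tests and the difference in scoring disappears.

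This reply stands in part. It means that biased measurement is not established, only that it follows if the scoring text is applied as written. It does not remove the conflict, because that text is the only one specific to CAB scoring and nothing says that it is set aside.

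Three stronger inferences are tempting, and the documents do not support them:

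- **Control change is zero by construction.** This is only one possibility; the protocol does not say how a control's post-test CAB would be produced.
- **At least 120 game plays feed the experimental score** (40 sessions × 3 games). The three-game, 15-minute session comes from Phase I. Phase III session length awaits the Phase I result, 40 sessions are only expected, and imperfect adherence is anticipated. Nor does the text say that every play enters the score. So 120 is not a minimum.
- **The trial's efficacy result is compromised.** The CAB is secondary. The PSQI, ISI, WHOQOL-BREF and PROMIS items are questionnaires that the update does not touch. The same holds for the BRIEF-A, and for sleep quality as the regression's dependent variable.

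**Conclusion.** The point holds as a contradiction with a conditional consequence. The scoring text and the assessment text disagree on how the post-baseline CAB is obtained. If the scoring text governs, measurement method is tied to arm in Phase III. Bias toward the trained arm is then likely, because practice on the games would be credited as cognitive gain in that arm only. The direction is an inference and the size is unknown; the illustrative 19%, 37% and 78% rest wholly on assumed shifts of 0.2, 0.3 and 0.5 SD.

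The affected analyses are the secondary CAB Group-by-Time comparison, the CAB part of the last regression step, and the Phase II CAB series from Day 3 on (scoring change and practice only). This should be fixed before the trial starts: if controls are not given the battery at post-test, no later analysis can recover the comparison. Because the outcome is secondary, it does not threaten the primary conclusions.

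**What to change.** Reconcile the Cognitive Skills, Phase III and Phase II sections by stating that:

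1. at post-test both arms take the full 17-test CAB afresh, under the same conditions as at pretest;
2. only these stand-alone scores enter the mixed models and the hierarchical regression;
3. the platform's automatically updated score is excluded from every analysis;
4. the same rule applies at each Phase II time point where the CAB is analysed.

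The cost is a change of wording and about 40 minutes per participant at the Phase III post-test, which the complete evaluation already implies. In Phase II, if the CAB is analysed at all seven assessments after Day 1, the time is 7 × 40 = 280 minutes per patient; the text on identical assessments already implies this too. The documents do not say whether the platform can report a fresh score separately from the updated one, so the sponsor should confirm this first.

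One limit remains. A fresh battery equalises the scoring but may not remove all practice gain if the games resemble the tests. CAB gains should be reported with that caveat.
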